## Abstract

**Background:**

A total of 22 priority countries have been identified by the WHO that account for 90% of pregnant women living with HIV. Nigeria is one of only 4 countries among the 22 with an HIV testing rate for pregnant women of less than 20%. Currently, most pregnant women must access a healthcare facility (HF) to be screened and receive available prevention of mother-to-child HIV transmission (PMTCT) interventions. Finding new approaches to increase HIV testing among pregnant women is necessary to realize the WHO/ President's Emergency Plan for AIDS Relief (PEPFAR) goal of eliminating new pediatric infections by 2015.

**Methods:**

This cluster randomized trial tests the comparative effectiveness of a congregation-based Healthy Beginning Initiative (HBI) versus a clinic-based approach on the rates of HIV testing and PMTCT completion among a cohort of church attending pregnant women. Recruitment occurs at the level of the churches and participants (in that order), while randomization occurs only at the church level. The trial is unblinded, and the churches are informed of their randomization group. Eligible participants, pregnant women attending study churches, are recruited during prayer sessions. HBI is delivered by trained community health nurses and church-based health advisors and provides free, integrated on-site laboratory tests (HIV plus hemoglobin, malaria, hepatitis B, sickle cell gene, syphilis) during a church-organized ‘baby shower.’ The baby shower includes refreshments, gifts exchange, and an educational game show testing participants’ knowledge of healthy pregnancy habits in addition to HIV acquisition modes, and effective PMTCT interventions. Baby receptions provide a contact point for follow-up after delivery. This approach was designed to reduce barriers to screening including knowledge, access, cost and stigma. The primary aim is to evaluate the effect of HBI on the HIV testing rate among pregnant women. The secondary aims are to evaluate the effect of HBI on the rate of HIV testing among male partners of pregnant women and the rate of PMTCT completion among HIV-infected pregnant women.

**Discussion:**

Results of this study will provide further understanding of the most effective strategies for increasing HIV testing among pregnant women in hard-to-reach communities.

**Trial Registration:**

Clinicaltrials.gov, NCT01795261

## Background

Globally, Sub-Saharan Africa (SSA) accounts for 76% of all women living with HIV and an estimated 90% of the 3.4 million children living with HIV. A total of 22 priority countries have been identified by the WHO that account for 90% of pregnant women living with HIV. Nigeria is one of only 4 countries among the 22 with an HIV testing rate for pregnant women of less than 20%
[1,2]. Studies have shown that when HIV-infected women are treated with antiretroviral therapy and their infants receive antiretroviral (ARV) prophylaxis, mother-to-child transmission of HIV (MTCT) occurs in less than 1% of pregnancies
[3-6]. Despite the availability of simple, less expensive and highly effective ARV regimens capable of being implemented in resource-limited settings, 75,000 Nigerian infants were infected in 2010
[1,7]. During that year, only 14% of pregnant women were tested for HIV, while 9% of pregnant women living with HIV received WHO recommended antiretroviral (ARV) therapy, and only 11% of HIV-exposed infants received ARV prophylaxis for prevention of mother-to-child HIV transmission (PMTCT) resulting in an estimated 75,000 HIV-infected infants in 2010
[1,8]. Currently, most pregnant women must access a healthcare facility (HF) to be screened and receive available PMTCT interventions. This clinic-based approach is challenging when only 35% of pregnant women deliver in an HF and only 2.9% of HFs have an established PMTCT program
[8,9]. Finding new approaches to translate evidence-based interventions in PMTCT to sustainable community-based programs is necessary to realize the WHO/PEPFAR goal of eliminating new pediatric infections by 2015
[10].

Various reasons have been identified as barriers to HIV testing and PMTCT completion. Low perception of personal risk, poor access to testing sites, cost, confidentiality, and HIV-related stigma have all been identified as barriers to HIV testing
[11-14]. Barriers to optimal PMTCT exist at the level of the patients and providers, but barriers at the health systems level appear to have more adverse impact on healthcare in general
[15-17]. Most women in Nigeria do not access prenatal care early in pregnancy, and only 35% of pregnant women deliver in a health facility where just 2.9% have an established PMTCT program
[9,18,19]. When community testing has been implemented to increase testing rate, the extensive attrition that takes place between HIV testing and treatment leads to people informed of their HIV-positive status failing to be adequately linked with appropriate services
[20].

The late initiation of prenatal care results in missed opportunities for repeat testing, an important factor in PMTCT, as a significant proportion of pregnant women are in HIV-discordant relationships and testing rates are low among adult males, which could result in sero-conversions late in pregnancy
[21-24]. Failure to disclose HIV sero-status is another barrier that hinders PMTCT completion, as studies have shown that women who do not disclose their sero-status to their male partners are less likely to complete interventions for PMTCT
[25-27]. Male partner involvement has been shown to positively impact PMTCT, but asking or requiring pregnant women to recruit their male partners for HIV testing creates a barrier to partner testing, even though there is an increased willingness to test for HIV when pregnant women are tested at the same time with their male partners
[28-31]. Despite these barriers, HIV testing exceeds 80% when pregnant women become aware of the effectiveness of interventions that assist in preventing MTCT and testing materials are available even in the presence of high anticipations of HIV/AIDS stigma
[32-35].

Three viable and potentially cost-effective strategies for mitigating systems-level barriers to optimal testing and PMTCT completion include: decentralizing testing beyond health facilities
[36,37], improving access to testing and treatment services, and identifying other delivery models that reduces loss to follow-up by linking testing sites to treatment centers
[38-41].

Finding new approaches to translate evidence-based PMTCT programs to community-based settings is necessary if we are to realize the PEPFAR goal of 80% HIV screening rate among pregnant women by 2015
[10]. Fortunately, the government of Nigeria, in its 2010–2015 National Strategic Framework (NSF), identified reduction in new infections as a major goal
[42]. It plans to increase access to quality HIV testing and ARV treatment for at least 80% of HIV-infected pregnant women. To achieve this, the framework calls for strengthening private sector engagement in expanding PMTCT interventions to community-based programs to complement existing clinic-based testing.

This study is one of few cluster randomized clinical trials of the effectiveness of congregation-based approach in hard-to-reach rural communities. We are reporting this method because it could serve as a model for other interventions aimed at improving maternal-child health outcomes in these communities.

### Study aims and hypothesis

The objective of this trial is to test the comparative effectiveness of a congregation-based Healthy Beginning Initiative (HBI) that promotes individual testing and utilizes the church network for subject tracking and retention versus a clinic-based approach in increasing HIV testing and PMTCT completion among 2,700 pregnant women and male partners attending 40 churches in Southeast Nigeria. We considered randomizing each individual patient, but the likelihood of contamination poses a threat to internal validity; thus, individual pregnant women will be nested within the church. We also considered a crossover design, but the possibility of withdrawing an intervention if it becomes effective would make this design problematic.

### Primary aim

The primary aim is to evaluate the effect of HBI on the HIV testing rate among pregnant women.

### Secondary aims

The secondary aims are to evaluate the effect of HBI on the rate of HIV testing among male partners of pregnant women and the rate of PMTCT completion among HIV-infected pregnant women.

### Hypotheses

We hypothesized that pregnant women randomized to the intervention group (IG) compared to those randomized to control group (CG) will have a higher rate of HIV testing, a higher rate of HIV testing among male partners, and a higher PMTCT completion rate among HIV-infected pregnant women. This study is one of few randomized trials to test the effectiveness of such a congregation-based approach in rural hard-to-reach communities.

## Methods

### Study design

Using a two-arm cluster randomized trial design, we will evaluate the effect of a congregation-based HBI that provides free, integrated on-site laboratory tests during a church-organized baby shower as the IG versus clinic-based approach as the CG on the rate of HIV testing among pregnant women, their male partners, and the PMTCT completion rate among HIV-infected pregnant women. A total of 40 churches in Enugu State, south-east Nigeria, will be randomly assigned to either the IG (N = 20 churches) or the CG (N = 20 churches). A total of 2,700 pregnant women will be enrolled in this study, with about 8 to 16 pregnant women each month per church (depending on the size of the church) enrolled each month over a 5-month period. Participants in churches randomized to the CG will be referred to the closest healthcare facility for HIV testing and prenatal care. Participants in churches randomized to IG will receive health education and be offered an HIV test as part of an integrated laboratory test on-site at the church during a baby shower program. The primary outcome is difference in the rate of HIV testing between both groups. The secondary outcomes are the difference in the rate of HIV testing among male partners, and the PMTCT completion rate among HIV-infected pregnant women in both groups. Pregnant women will complete an investigator-administered questionnaire to collect information on HIV testing and PMTCT completion. Self-reported HIV testing and PMTCT completion will be confirmed with the healthcare facility for participants in churches randomized to the CG, and with on-site HIV testing data and the healthcare facility (PMTCT completion) for participants in churches randomized to the IG (Figure 
1). Participants in churches randomized to CG will have two study visits: baseline (recruitment) and six to eight weeks after delivery. Participants in churches randomized to IG will have three study visits; baseline (recruitment), baby shower and six to eight weeks after delivery.

**Figure 1 F1:**
[figure not shown]
Overview of the healthy beginning initiative.

### Study setting and participants

We selected Enugu State as the site for the proposed study for three reasons: first, its population is culturally and ethnically related and predominately Christian, with church attendance approaching 90%
[43,44]. Second, the overall state HIV sero-prevalence of 5.1% is close to the national average of 4.1%
[8]. Third, the churches that we propose to use as study sites are widely distributed in Enugu and Oji-River areas, and represent variations in the prevalence rate across the state of 4% to 8% (6% average)
[8]. Any self-identified pregnant woman attending any of the study sites is eligible to participate. Women are encouraged to participate with their male partners, but can still participate if the male partner chooses not to participate. The study was approved by the Institutional Review Board of the University of Nevada, Reno, and the Nigerian National Health Research Ethics Committee.

### Church recruitment and randomization

Recruitment occurred at the level of the churches and participants (in that order), while randomization occurred only at the church level. A total of 40 churches selected from four dioceses (the Anglican diocese of Enugu, the Catholic diocese of Enugu, the Anglican diocese of Oji-River, and the Catholic diocese of Agwu) were randomized to either the IG or the CG. All of the bishops who oversee churches in the proposed study areas had previously agreed to participate in this study and gave the study team access to speak to the priests under their dioceses. Randomization of churches occurred in 4 cohorts of 10 churches following random ranking. The churches were randomized in a 1:1 ratio to either the IG or CG. The sequence of randomization was generated by [name] and kept in a sealed opaque envelop away from the study sites in accordance with CONSORT guidelines
[45]. Once the sites had been recruited and baseline information on churches collected (*e.g.*, type, size of congregation), the sites were informed of their randomization group and assigned a code. Because of the nature of the intervention, it was impossible to blind the participants, community health nurses, lay health advisors, and study coordinators to the group assignment, but the test results cannot be influenced by the study coordinators.

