### Sample size and power analysis

The proposed study is a two-arm cluster randomized controlled trial with the church as the unit of randomization. Thus, there are two important sample size estimates: N, the number of pregnant women; and K, the number of churches, with the pregnant women nested within the K churches. We reviewed the total annual infant baptisms in churches located in Enugu and Oji-River for 2010 to estimate the potential number of pregnant women. Our review indicated that there were 20,700 infant baptisms conducted in 2010. Further analysis showed that in 2010, Enugu and Oji-River each contained about 50 churches that had 200 infant baptisms and 40 churches that had at least 100 infant baptisms (Table 
1).

**Table 1 T1:** Infant baptisms in churches

**Enugu Local Government Area**	**Oji-River Local Government Area**
Catholic Churches: 9,300 infant baptisms	Catholic Churches: 9,000 infant baptisms
Anglican Churches: 1,400 infant baptisms	Anglican Churches: 1,000 infant baptisms

Power calculations were performed using the module ‘Inequality Tests for Two Proportions in a Cluster-Randomized Design’ in PASS 11, which implements methods of Donner and Klar
[46]. That module approximates power for simple two-sample binomial tests for data collected in clusters with non-zero intra-cluster correlation (ICC). The Proc GLIMMIX analysis should have superior power since inclusion of covariates should reduce variability. For all three hypotheses, there will be 40 clusters (churches). For all three, there is an anticipated Control Group rate between 15% and 25%
[1,8]. The usual recommendation is to take ICC between 0.002 and 0.05; ICC as high as 0.10 is considered quite high. The PASS module chooses a cluster size (number of individuals per cluster), which determines the total sample size as cluster size X, no. of clusters. Table 
2 shows minimum detectable Intervention Group rates for various cluster sizes, Control Group rates, and ICC. The total sample size is driven by Secondary Hypothesis 2, where the CG rate should be around 0.20, and the intervention is expected to more than double the rate. From the preceding Table 

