### Statistical methods

All three hypotheses test for differences in two binomial proportions at follow-up. Clustering effects must be incorporated in the analysis since data collected on parishioners within the same church could be expected to exhibit correlation, while data collected on parishioners in different churches should exhibit minimal correlation. Generalized linear mixed models as implemented in PROC GLIMMIX in SAS 9.3
[47] provide a rich set of tools for analyzing such data. Data will be analyzed with that procedure using a logit link function and the binomial distribution. These are multilevel models allowing incorporation of covariates and confounders for the individual (such as age, household income, education level, previous HIV testing, last menstrual period, marital status, employment status, male’s partners’ previous HIV test results, and situational/contextual factors) and cluster-level (*i.e.*, church) covariates and confounders such as size of church and congregation type (Anglican or Catholic). For all three hypotheses, a preliminary (and similar) analysis will model the probability that an individual declines participation; any significant predictors from that model will be used in the main analysis to reduce confounding. Statistical significance will be set as p-value <0.05 and tests will be 2-sided.

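### The church-level covariates named for the mixed model include neither randomisation cohort nor geographic area; both should be prespecified, for a gain in precision that ranges from nil to moderate

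*Protocol article*

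**What the plan says.** Under Church recruitment and randomization, the protocol article gives the source of the churches ("A total of 40 churches selected from four dioceses"), the batching ("Randomization of churches occurred in 4 cohorts of 10 churches following random ranking") and the ratio ("The churches were randomized in a 1:1 ratio to either the IG or CG"). Two dioceses are Anglican and two Catholic, and for each denomination one is Enugu and the other Oji-River or Agwu. The section does not say that the cohorts were dioceses or areas, and it does not state a 5:5 split within each cohort.

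Under Statistical methods, the model is a generalised linear mixed model: "Data will be analyzed with that procedure using a logit link function and the binomial distribution". The church-level terms are introduced as "covariates and confounders such as size of church and congregation type (Anglican or Catholic"). Cohort, diocese and area are not named. Significant predictors from a preliminary model of declining participation will also enter the main analysis.

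Under Study setting and participants, the churches are described as spread over the Enugu and Oji-River areas, and are said to "represent variations in the prevalence rate across the state of 4% to 8% (6% average").

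**The concern.** A factor used to restrict randomisation normally belongs in the analysis. If allocation is balanced within blocks and the blocks differ in outcome, the arm comparison is free of block differences, but a model without the blocks still counts them in the church random effect. The reported standard error is then too large and the test conservative. With 40 churches this can matter, because between-church variation may be a large part of the error.

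Area raises a separate question. Control women are referred to the nearest health facility, so control testing may depend on local access. Denomination cannot stand in for area, because each denomination is present in both. No stratification by area is described, so the arms could differ in area mix by chance.

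The rule for adding predictors of declining participation does not ensure that either factor enters the model. At stake is precision, and a covariate set fixed before the data are analysed; the validity of the test is not in question.

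**Working it through.** **Inputs from the protocol article.** 40 churches, 20 per arm; 2,700 women, so 2,700/40 = 67.5 per church; 140 HIV-infected women, so 140/40 = 3.5 per church for PMTCT; control rate 0.15 to 0.25; ICC usually 0.002 to 0.05, with 0.10 described as quite high; two-sided 5% test.

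**Assumed, because the article does not give it.** f, the share of between-church variance explained by cohort or area.

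**The plan's own figure.** Table 2 (cluster size 50, control rate 0.20, ICC 0.05) gives a detectable rate of 0.30. Effective n per arm = 20 × 50/(1 + 49 × 0.05) = 1,000/3.45 = 289.9. SE = √[(0.20 × 0.80 + 0.30 × 0.70)/289.9] = 0.0357. Then 0.10/0.0357 − 1.96 = 0.84, which is 80% power. The power level is not printed, but at 80% with unpooled variance all 45 cells reproduce within 0.005. The table uses no covariates.

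**Case 1: a factor balanced by design (cohort, if 5:5).** The variance of a church mean is proportional to V = ICC + (1 − ICC)/m. Including the factor lowers it to V − f × ICC. The overstatement of the SE when it is left out is √[V/(V − f × ICC)].

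| m | ICC | V | f = 20% | f = 40% |
|---|---|---|---|---|
| 67.5 | 0.002 | 0.0168 | 1.2% | 2.5% |
| 67.5 | 0.05 | 0.0641 | 9% | 21% |
| 67.5 | 0.10 | 0.1133 | 10% | 24% |
| 3.5 | 0.05 | 0.3214 | 1.6% | 3.3% |
| 3.5 | 0.10 | 0.3571 | 2.9% | 6.1% |

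Example: at m = 67.5 and ICC 0.05, the ratios (V − f × ICC)/V are 0.0541/0.0641 = 0.844 and 0.0441/0.0641 = 0.688; √(1/0.844) = 1.09 and √(1/0.688) = 1.21.

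As a detectable rate (control 0.20, ICC 0.05, m = 67.5, 80% power, pooled variance), 0.297 becomes 0.293, 0.286 or 0.274 for f = 10%, 25% or 50%.

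The effect on the test was simulated with 40 church means in four blocks of ten, split 5:5, and 40,000 runs. Here f is a share of the variance of church means, which is not the same as f above.

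| f | Type I error, blocks ignored | Power, ignored | Power, adjusted |
|---|---|---|---|
| 0 | about 5% | 0.800 | 0.798 |
| 10% | 4.2% | 0.817 | 0.837 |
| 25% | 3.0% | 0.848 | 0.899 |
| 50% | 1.5% | 0.896 | 0.977 |

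Adjusted type I error is about 5% throughout. The row f = 0 represents cohorts that are random subsets with no timing effect.

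**Case 2: a factor not balanced by design (area).** Assume 20 churches per area and a 20/20 allocation not stratified by area. By the hypergeometric distribution, the arms differ by 4 or more churches from one area with probability 34%, and by 6 or more with probability 11%. Simulating a four-level factor that does not restrict allocation, with f = 25%, type I error is about 5% with or without adjustment, and power is 0.825 unadjusted against 0.871 adjusted. Chance imbalance is therefore already inside the test's error rate, and adjustment offers precision only.

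Both cases treat proportions as approximately linear; the planned model is on the logit scale, so the figures are approximate.

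**The case against.** The strongest reply is that the covariate list is illustrative. The article writes "covariates and confounders such as size of church and congregation type (Anglican or Catholic"), also allows situational and contextual factors at the individual level, and condenses a fuller plan. This stands: a reader might infer that the model excludes cohort and diocese, but the text shows only that they are not named. Diocese is also half covered already, because denomination is listed; the unnamed half is area.

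Second, the batching followed a random ranking. If that ranking formed the cohorts, they have no built-in relation to testing, and adjustment gains nothing unless timing matters. This also stands. The article reports early shortages of forms and blood-collection kits, which would give cohort a timing effect if the cohorts opened in sequence, but it does not say that they did.

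Third, the argument about an inflated standard error needs a factor balanced by design. Only cohort could be one, so the 9% to 21% should not be read across to area. A reader might also infer that chance imbalance in area would confound the result. It would not bias a randomised comparison, as Case 2 shows.

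Fourth, the 4% to 8% spread is HIV prevalence, not testing uptake, and the article gives no separate Enugu and Oji-River figures. That area predicts testing is plausible but not shown.

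Finally, the article considers the women's and partners' comparisons amply powered, so a modest loss of precision is unlikely to decide them. What the reply leaves untouched is that the grouping by which churches were randomised is absent from the named terms, and that adding it is nearly free.

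**Conclusion.** The point holds as a modest improvement to the analysis. Cohort and area are not among the named church-level covariates. Omitting a balanced, predictive cohort would make the test conservative and would not inflate the type I error. Omitting area forgoes possible precision and introduces no bias.

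The size cannot be fixed from the article. It runs from nil (cohorts unrelated to testing), through about 1% to 2.5% of the standard error at ICC 0.002, to about 9% to 21% at ICC 0.05. The non-zero figures assume a factor balanced across arms that explains 20% to 40% of between-church variance beyond the covariates already named. For PMTCT, with about 3.5 women per church, the same shares give at most about 6%, even at ICC 0.10.

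**What to change.** State in the analysis plan, before the data are analysed, that the primary GLIMMIX models for women's and partners' testing will include:

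- randomisation cohort (four levels) as a fixed effect;
- diocese (four levels) in place of the Anglican/Catholic term, since it carries both denomination and area;
- church size, as now.

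If cohort and diocese coincide, include only one. The article should also state whether each cohort was split 5:5 and how the ranking formed the cohorts.

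The cost is a line of model code; cohort is fixed by the randomisation and diocese is known for every church. Cohort uses 3 degrees of freedom, and diocese uses 3 where denomination used 1, so the net cost is 3 + 2 = 5 of about 38 (40 churches less 2 arms). If balanced cohorts turn out not to predict testing, the simulated power cost of the cohort term is negligible (0.800 to 0.798). Diocese is not described as balanced by design, so that term could cost a little more power if it does not predict testing. Fixing the terms in advance also removes a later choice from an open list in an unblinded trial.
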